#### Primary outcome

The primary outcome is the amount of time in minutes per day that is spent engaging in social activities, on average, over the previous 4 days. It is assessed using a shortened version of the TUS, developed by the Office for National Statistics (ONS) to examine how the general population in the UK spend their time. The measure has been previously used with patients with schizophrenia.^10^ The present version excludes any items related to social media interaction. A period of 4 days allows sufficient time for increased social activity to be detected, with reduced risk of recall bias.

#### Secondary outcomes

The number of social contacts over the previous 4 days is assessed using the 16-item patient-rated Social Contacts Assessment (SCA; D Giacco, C Palumbo, N Strappelli, *et al*. Objective social isolation and loneliness in patients with psychotic and mood disorders. *Compr Psychiatry* under review).Subjective quality of life is assessed using the Manchester Short Assessment of Quality of Life (MANSA).^11^The objective social situation is assessed using the Objective Social Outcomes Index (SIX).^12^Both patient and volunteer self-esteem are assessed using the 20-item Self-Esteem Rating Scale—Short Form (SERS-SF).^13^The therapeutic relationship will be assessed using the Scale to Assess Therapeutic Relationships in Community Mental Health Care (STAR).^14^ Only patients in the intervention arm and their volunteers will complete this, 6 and 12 months after beginning the intervention. Patients will complete the patient version of the scale (STAR-P) while volunteers will complete an adapted version (STAR-V) of the clinician scale (STAR-C).Attitudes towards mentally unwell people will be assessed in volunteers using the Social Distance Questionnaire;^15^ and the Community Attitudes toward the Mentally Ill scale (CAMI).^16^

#### Clinical symptoms

Patients' positive and negative symptomatology is assessed on the Positive and Negative Syndrome Scale (PANSS),^17^ a 30-item observer-rated measure, and the Clinical Assessment Interview for Negative Symptoms (CAINS),^18^ a 13-item observer-rated measure of negative symptoms.Patients' level of depression is measured using the Beck Depression Inventory (BDI).^19^*Costs*: Service use and costs are assessed using the Client Service Receipt Inventory (CSRI).^20^ Quality of life-adjusted years (QALYs) are calculated based on the EQ-5D-5L.^21^

In addition, demographic information is collected at baseline. The number of meetings between each volunteer–patient pair and the amount of time spent together during each meeting is documented throughout the study.

### Qualitative data

At the end of the intervention, 20 patients in the intervention group and 20 volunteers will be asked to complete semistructured, in-depth interviews about their experiences of the scheme. We will employ purposive sampling to capture patients who completed the intervention as well as those who showed irregular patterns in meeting with volunteer. The interviews will be audio-recorded, transcribed and analysed using the thematic analysis framework proposed by Braun and Clarke.^22^ Participants will be paid £15 for their participation in the interviews.

### Assessment procedures

All researchers involved in data collection both prior and after intervention allocation are blinded for the duration of the trial, while it will not be possible to patients, volunteers, clinicians and researchers involved in the intervention delivery to be blinded to the allocation The only exception to this is data collection for the STAR-P and STAR-V, as these assess the relationship between the patient and the volunteer, which applies to the intervention group only. These assessments are carried out via phone by unblinded researchers involved in the delivery of the intervention.

There is a considerable risk of researchers becoming unblinded during follow-up assessments due to patients in the experimental group mentioning activities with the volunteer. To limit this risk, prior to each interview, patients receive instructions to avoid revealing their allocation. In addition, at the end of the interviews, researchers record their guesses as to whether patients are in the intervention or the control group.

There is also a risk that some measures are inflated in the intervention group by the intervention itself, that is, increased social activity as a direct result of meetings with the volunteer. To address this, unblinded researchers liaise with volunteers to ensure that no meeting takes place between the patient and the volunteer in the week prior to the follow-up assessment.

Guidance on assessment where participants provide ambiguous answers (eg, patients reporting having spent between 1 and 2 hours engaging in activities) has been developed and is adhered to by all researchers. Inter-rater reliability across researchers involved in data collection is established for PANSS and CAINS prior to first assessment.

All quantitative data are entered into Access databases, and will be retrieved for data cleaning before statistical analyses. Any personal information stored in locked cabinets on NHS premises if in paper version, and encrypted if in electronic version.

## Randomisation

Following baseline assessments, eligible patients are randomised either to the intervention condition or the active control condition, using a 1:1 block design algorithm via the online randomisation site of the registered Pragmatic Clinical Trials Unit (PCTU) at Queen Mary University of London. A one-off meeting is then arranged by an unblinded researcher to inform a patient of his or her allocation.

## Proposed sample size

Previous unpublished work within the wider research programme surveying 113 patients with psychosis in secondary care in East London has shown that patients tend to spend 327 min per week on average engaging in social activities (SD=480), or ∼45 min per day. Doubling this to 90 min per day would be equivalent to an effect size of 0.6 (Cohen's d). To detect such an effect on a 5% significance level with 80% power, data for 84 patients (2×42) are required. Assuming a 20% drop out rate between baseline and 1-year follow-up (as observed in similar trials with similar patient populations),^23^ a total sample size of 106 is needed.

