## Methods

### Study setting and design

This is a parallel group exploratory RCT with 1:1 allocation ratio testing the effectiveness of volunteer support, specifically for patients with psychotic disorders with limited engagement in social activities. The trial compares the intervention, regular one-to-one support from a volunteer, to an active control condition in which there is no support from a volunteer. Data are collected at baseline, 6 and 12 months (figure 1). Researchers conducting outcome assessments will be blind to the allocation of patients. All the statistical analyses will be conducted blind to the participant allocation. The trial is conducted within community mental health setting in the UK.

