## Statistical analysis

### Quantitative assessments

All statistical analyses will be described in a statistical analysis plan, which will be finalised and agreed prior to any analysis or unblinding of the data. Outcomes will be compared between the intervention and control groups using linear regression models, adjusting for the baseline score of the given outcome.

All analyses will be conducted under the intention-to-treat principle, and significance testing will be at the 5% level (two-sided). Results will be presented in line with the recommendations given in the CONSORT statement extension for the reporting of RCTs.

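### The printed mean and SD give a standardised effect of about 0.66, not the stated 0.6, so the sample-size figures need one consistent restatement (minor)

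*Protocol article*

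**What the plan says.** All planning figures are in the Proposed sample size section of the protocol article. An unpublished survey of 113 patients gave "327 min per week on average engaging in social activities (SD=480"), which the section restates as roughly 45 min per day. The target follows: a doubling, to 90 min per day, "would be equivalent to an effect size of 0.6". The size is then derived: "To detect such an effect on a 5% significance level with 80% power", "data for 84 patients (2×42) are required". Allowing for 20% drop-out, the total becomes 106.

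Two further inputs stand elsewhere. Quantitative assessments says that "significance testing will be at the 5% level (two-sided"), and Study setting and design describes a "parallel group exploratory RCT with 1:1 allocation ratio". The analysis model is linear regression adjusted for the baseline score. The sample-size section gives no baseline–outcome correlation, no other SD and no formula.

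**The concern.** The section prints a mean, an SD, a target difference and a standardised effect, so the last can be checked against the others, and it does not match. The number of patients matches neither the d obtained from the mean and SD nor a d of exactly 0.60.

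At stake is how the planning figures are reused. The Discussion presents the trial as a possible basis for a larger definitive one. Someone who carries forward d = 0.6, and someone who carries forward 45 min per day with an SD of 480 min per week, would be using different targets while believing them to be the same.

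**Working it through.** **Inputs.** Mean 327 and SD 480 min per week; rounded mean 45 and target 90 min per day; stated d = 0.6; 5% significance; 80% power; 42 per arm; 20% drop-out (all from Proposed sample size). Two-sided testing (Quantitative assessments). 1:1 allocation (Study setting and design).

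**Step 1: the drop-out step reproduces.** 84/(1 − 0.20) = 105, made even for 1:1 allocation = 106.

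**Step 2: the effect size does not.**
- Daily mean: 327/7 = 46.7 min. Daily SD: 480/7 = 68.6 min.
- Rounded figures: d = (90 − 45)/68.6 = 0.656.
- Unrounded figures: d = 327/480 = 0.681.
- For d = 0.6, a 45-minute difference would need an SD of 45/0.6 = 75 min per day, that is 525 min per week, which is not stated.

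**Step 3: the patients needed.** By normal approximation, n per arm = 2(1.960 + 0.842)²/d². At d = 0.60 this is 43.6, rounded up to 44. The two-sample t-test (noncentral t) gives 44.6, rounded up to 45. Across the candidate values of d:

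| d | Source | n per arm for 80% power: normal / t-test | Power at 42 per arm: normal / t-test |
|---|---|---|---|
| 0.600 | as printed, read as exact | 44 / 45 | 78.5% / 77.6% |
| 0.656 | 45/68.6 | 37 / 38 | 85.3% / 84.4% |
| 0.681 | 327/480 | 34 / 35 | 87.7% / 87.0% |

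**Step 4: which d gives 42 per arm?** Solving for 80% power at n = 42 gives d = 0.611 (normal approximation) or 0.619 (t-test). With SD 68.6, the t-test value is 0.619 × 68.6 = 42.4 min per day.

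**Step 5: other routes to 42.** At d = 0.6, a one-sided test needs 35 per arm and 90% power needs 59, so neither explains it (both by normal approximation). Going from the unrounded 46.7 to the rounded 90 min per day gives d = (90 − 46.7)/68.6 = 0.631 and 41 per arm by t-test. That is close to 42, but it is not a doubling.

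**The case against.** The strongest reply is that 0.6 is printed to one decimal. A d of 0.61 to 0.62 prints as 0.6 and gives 80% power with 42 per arm. This stands. A reader might infer that 2×42 contradicts d = 0.6; at the printed precision it does not. Even with d taken as exactly 0.600, the shortfall is 1.5 to 2.4 percentage points of power, or two to three patients per arm. Rounding does not rescue the step before, because 0.656 and 0.681 both round to 0.7.

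Baseline adjustment could also close the gap at d = 0.600. With an assumed baseline–outcome correlation of 0.2, which the protocol does not state, the normal-approximation requirement is 43.6 × (1 − 0.2²) = 41.9, or 42 per arm. The sample-size section does not invoke adjustment, and adjustment would not turn 45/68.6 into 0.6.

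It may be said that a weekly SD divided by 7 is not the SD of the four-day average that forms the primary outcome. That is fair, and no SD for that average is given. But d = 0.6 would need a larger SD (75 min per day), whereas the Discussion expects the four-day window to reduce variance.

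Finally, the trial is described as exploratory, and the Discussion calls the expected effect sizes speculative. This bears on how serious the point is, not on whether the figures agree.

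**Conclusion.** The point holds as a minor correction of stated planning figures. The effect size is wrong as written: the printed mean and SD give d = 0.66 (0.68 unrounded), not 0.6. The 84 completers fit a d of about 0.62, which the stated mean and SD do not yield.

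Two stronger conclusions that a reader might draw are not supported. First, the trial is not underpowered on its own inputs: with the stated mean and SD, 42 per arm gives 84% to 87% power by t-test, because the planned d is smaller than the one those inputs imply. Second, a null result would not become uninterpretable. The target is stated in minutes per day, and such a result would be read from the estimated difference and its confidence interval on that scale. The ambiguity is confined to the standardised form, between 0.6 and 0.68.

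These power figures assume an unadjusted two-sample t-test, a two-sided 5% level, equal arms, and the survey SD carried over to the trial. That last assumption is the protocol's own and cannot be checked here. The survey covered patients with psychosis in secondary care generally, while the trial admits only those with less than 60 min of social activity per day.

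**What to change.** Keep N = 106 and replace the effect-size and power statement with one consistent set, for example:

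> A difference of 45 min per day with an SD of 68.6 min per day (480/7) corresponds to d = 0.66. With 84 completers (2×42), power is about 84% at a two-sided 5% level (unadjusted t-test), and 80% for d of about 0.62 (about 42 min per day).

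If d = 0.6 was the intended target, state instead that 84 completers give about 78% power by unadjusted t-test. If the sponsor used another SD or allowed for baseline adjustment, print that SD or the assumed correlation.

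The cost is one sentence in the sample-size section, carried into the statistical analysis plan if it repeats these figures. No patients are added and no analysis changes.

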## Data monitoring

All data are stored in accordance with the Data Protection Act 1998 and accessible only to members of the research team. Patient-identifiable data are anonymised and password-protected. The trial has no formal data monitoring; however, the Trial Steering Committee will provide input into data monitoring. No interim analyses will be carried out. No risk to participants is expected; however, any adverse events occurring during the study period will be recorded.

## Statistical analysis

### Quantitative assessments

All statistical analyses will be described in a statistical analysis plan, which will be finalised and agreed prior to any analysis or unblinding of the data. Outcomes will be compared between the intervention and control groups using linear regression models, adjusting for the baseline score of the given outcome.

All analyses will be conducted under the intention-to-treat principle, and significance testing will be at the 5% level (two-sided). Results will be presented in line with the recommendations given in the CONSORT statement extension for the reporting of RCTs.

#### Sensitivity analysis

Any outlying observations will be checked for data accuracy and may be excluded in a sensitivity analysis. Individuals may drop out of the intervention or be lost to follow-up. In these cases, assumptions must be made about their outcome data. One may argue that patients who drop out are more likely to do so if they do not perceive benefit of the intervention, and most likely would have ended with a less favourable outcome had they stayed in treatment. Yet, this is not necessarily so for patients with severe symptoms of schizophrenia. They might also tend to drop out when they perceive improvement and no further need for the treatment (in this trial, meetings with a volunteer), in which case drop outs would have ended with more favourable outcomes. Sensitivity analyses for both scenarios will be explored. Depending on data available, we will also conduct a per protocol analysis.

The final data set will be accessible to the principal investigator and the trial statisticians.

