### Planned interventions

#### Experimental intervention

This consists of individual patients with psychosis being enrolled in a companion scheme, whereby they are matched with a volunteer companion, who will provide one-to-one support on a weekly basis over a 1-year period. This is in addition to their treatment as usual. The main aim of the scheme is to gradually develop a trusting relationship and motivate patient to engage in social activities within local community. This will involve chatting over a cup of tea at the beginning and develop into more active social engagement such as attending workshops and events available in the local area according to patient's interests. The companion scheme is a complex intervention comprising the recruitment of suitable volunteers, their training and supervision (described below), and the regular contact between them and the patients. The format of the scheme has been informed by interviews with participants in existing befriending schemes (befrienders, befriendees and coordinators of schemes) as part of the wider research programme.

For each patient–volunteer pair, the volunteer coordinator attempts to create a match based on common interests and individual preferences, as well as practical considerations such as distance and mutual availability. A meeting is arranged to introduce the pair at the patient's home, unless the patient wishes for the meeting to take place elsewhere. This is treated as a ‘test meeting’, after which the volunteer coordinator confirms with both parties separately that they are willing to proceed with the match. The volunteer coordinator facilitates the meeting by explaining the purpose of the meetings, boundaries and ground rules and establishing common interests among the two. Both parties are provided with an activity booklet detailing free or inexpensive facilities and activities available locally (eg, parks, community centres, libraries, sports, leisure centres, galleries and museums) and are encouraged to pursue these during their contact. It is reiterated that the pair should meet weekly for at least 1 hour, and that these meetings will continue for 1 year, after which they can decide whether or not they wish to continue to meet, without being overseen by the companion scheme.

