## Discussion

The present trial aims to provide evidence of the effectiveness and cost-effectiveness of one-to-one volunteer support for patients with psychosis. The trial is rigorously designed, including a well-defined and closely monitored intervention with systematic training and supervision of volunteers, an active control, and blinded outcome assessment.

Implementing the trial design has a number of challenges. Patients with psychotic disorders often have high levels of social withdrawal, but may not necessarily express a feeling of loneliness. Thus, their motivation to engage in social activities may be low, and they might either not be willing to establish a relationship with a volunteer or struggle to continue with regular meetings over a 1-year period. Matching of individual patients and volunteers is rather speculative, and there is no published research evidence available to guide this process. In addition, influencing the behaviour of volunteers with a view to improving patient outcomes may be more difficult to achieve than in trials targeting clinicians' actions.

There are also various challenges to the evaluation methodology. The primary outcome of assessing time spent on social activities might not capture the real extent of social isolation. The intervention may increase social activities, but ensuring that this increase is not inflated by the direct contacts with the volunteer may be difficult. Equally, patients' opportunity to socialise further may be restricted by the time spent with the volunteer. Measuring time use over the previous 4 days rather than the previous week may improve response validity, but reduce outcome variance.

The trial will assess a range of potentially important outcomes; however, it remains speculative as to what the most appropriate outcomes are and what effect sizes one may expect. As such, the trial remains exploratory in its nature, with the prospect of informing a larger definitive trial. The findings may help not only to test the effectiveness of the volunteering scheme, but also to understand better the underlying processes of potential changes in patients. The qualitative analyses accompanying the trial will be central to this.

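### A per-protocol analysis based on volunteer meetings would compare self-selected intervention patients with essentially unselected controls; a pre-specified complier-average analysis on the logged meetings is the better adherence analysis.

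*Protocol article*

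**What the plan says.** The main comparison, under Quantitative assessments, is by intention to treat: "Outcomes will be compared between the intervention and control groups using linear regression models, adjusting for the baseline score of the given outcome". The same section places all analyses under that principle and defers detail to a statistical analysis plan to be agreed before analysis or unblinding. Under Sensitivity analysis the article then adds: "Depending on data available, we will also conduct a per protocol analysis". It gives no per-protocol population, adherence criterion or comparator.

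Four other places bear on the point:

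- **Experimental intervention:** participants are told that "the pair should meet weekly for at least 1 hour, and that these meetings will continue for 1 year".
- **Active control condition:** controls get no volunteer. They get one booklet meeting with a researcher shortly after allocation.
- **Clinical symptoms** (closing paragraph): "The number of meetings between each volunteer–patient pair and the amount of time spent together during each meeting is documented throughout the study".
- **Discussion:** because motivation for social activity may be low, patients "might either not be willing to establish a relationship with a volunteer or struggle to continue with regular meetings".

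The article does not mention a complier-average or instrumental-variable analysis.

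**The concern.** Adherence to volunteer meetings can be observed only in the arm that is offered a volunteer. If the per-protocol set is defined by meetings attended, patients who did not meet leave the intervention arm, while the controls who would not have met stay in theirs. The balance created by randomisation is lost.

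The selection also acts close to the primary outcome. The Discussion links failure to meet with low motivation for social activity, and the outcome is minutes per day of social activity. A patient's tendency to adhere may therefore predict the outcome even if the scheme does nothing. A per-protocol estimate larger than the intention-to-treat estimate could then be read as the effect of the scheme when properly delivered, when part of it is selection.

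**Working it through.** The article gives no figure for this point, so there is none to reproduce. Adherence and its correlation with outcome are assumptions, shown as ranges.

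**Inputs**
- SD: 480 min per week (Proposed sample size), so 480/7 = 68.6 min/day.
- Target difference: 45 min/day, from 45 to 90 (same section).
- Evaluable patients: 42 per arm (same section).
- Assumed: proportion adherent p = 0.6 to 0.8; absolute correlation between propensity to adhere and outcome r = 0.2 to 0.4.

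**Step 1: bias of adherers against all controls when there is no true effect**

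If adherers are the top fraction p of a normal propensity, their mean outcome differs from that of the whole arm by

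bias (SD) = r × φ(c)/p, with c = z(1 − p), the standard normal quantile at 1 − p.

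| p | r | φ(c) | bias, SD | min/day (× 68.6) | share of 45 min | two-sided rejection rate |
|---|---|---|---|---|---|---|
| 0.8 | 0.2 | 0.280 | 0.070 | 4.8 | 11% | 6.1% |
| 0.7 | 0.3 | 0.348 | 0.149 | 10.2 | 23% | 9.5% |
| 0.6 | 0.4 | 0.386 | 0.258 | 17.7 | 39% | 17.6% |

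The rejection rate uses 42 controls and 42p adherers, with SE = √(1/42 + 1/(42p)) SD, against a nominal 5%. With r negative, the bias has the same size and the opposite sign, and the rejection rate is unchanged. These are unadjusted figures.

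**Step 2: cross-check by a second route**

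Bias = (prognostic gap between adherers and non-adherers) × (1 − p). With an assumed gap of 0.3 to 0.6 SD and the SD of 75 implied by d = 0.6 (45/0.6), p = 0.7 gives 0.3 × 75 × 0.3 = 6.8 to 0.6 × 75 × 0.3 = 13.5 min/day. Over p = 0.5 to 0.8 the range is 4.5 to 22.5. The two routes agree in size.

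**Step 3: what the alternative does**

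Complier-average effect = intention-to-treat effect / p. If patients classed as unexposed nevertheless gain e, it is too high by e × (1 − p)/p.

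Simulated means (42 per arm, SD 75, p = 0.7, true effect in adherers 45 min/day, 4,000 runs per scenario):

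| gap, SD | gain e in non-adherers | ITT | per-protocol | complier-average |
|---|---|---|---|---|
| 0.3 | 0 | 31.5 | 51.7 | 44.7 |
| 0.6 | 0 | 31.4 | 58.6 | 44.4 |
| 0.6 | 22.5 | 38.3 | 58.5 | 54.6 |
| 0 | 22.5 | 38.5 | 45.4 | 55.2 |

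The complier-average estimate removes the selection bias when unexposed patients gain nothing. When they do gain, it is biased: 22.5 × 0.3/0.7 = 9.6 min/day here, and with no prognostic gap it does worse than per-protocol. This is why the definition of exposure matters. A high cut-off leaves many patients with some meetings in the unexposed group, whereas at least one meeting leaves few who could gain from meetings.

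**Step 4: price in precision**

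Its standard error is about 1/p times that of intention to treat. At p = 0.7 that is 1/0.7 = 1.43; the simulation gave about 24 against 17 min/day, with per-protocol at about 18.

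**The case against.** The strongest reply is that the article does not define the per-protocol set. A reader might infer that poor adherers will be dropped from the intervention arm only and compared with every control, but that is not stated. The definition properly belongs to the analysis plan, and the control arm has a booklet meeting that could serve as a criterion. This stands, and the point is therefore conditional on a set built on meetings. The booklet meeting would not restore balance, however: missing one session does not identify the controls who would have failed a year of weekly meetings.

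A reader might also infer that the bias must favour the scheme. The documents do not support that. Sensitivity analysis says that patients may stop because they see no benefit or because they have improved, and excluding improvers would bias against the scheme. The Discussion makes the favourable direction the more likely one, in conditional language.

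A third tempting reading is that the decision to run the analysis depends on results. The wording refers to the availability of data, not to what the data show.

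The size can be disputed too. Adherence and correlation are assumed, and the planned baseline adjustment may shrink the bias. On the other side, eligibility below 60 min/day narrows the range of the baseline score and so limits what adjustment can remove.

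Finally, the complier-average analysis does not answer the identical question free of bias. It estimates the effect in patients who would meet a volunteer if offered one. It assumes that allocation acts only through meetings, and it does not repair outcomes lost to follow-up. If nearly everyone has one meeting, it will lie close to intention to treat. All of this stands and shapes the fix.

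**Conclusion.** The point holds in conditional form. A per-protocol analysis defined by meetings attended breaks randomisation in one arm, on a characteristic close to the primary outcome. Under 60 to 80% adherence and an absolute correlation of 0.2 to 0.4, both assumed, the unadjusted bias is about 5 to 18 min/day, or 11 to 39% of the 45-minute target. It is probably in favour of the scheme but possibly against it, and may be smaller after baseline adjustment.

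A reader might go further and infer that the trial's conclusion is at risk. It is not: the main comparison is by intention to treat, the per-protocol analysis is supplementary, and the trial calls itself exploratory. The rejection rates above have no decision role. What is at stake is how the adherence result is interpreted.

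**What to change.** Pre-specify a complier-average causal effect analysis in the statistical analysis plan, in place of the per-protocol analysis or as the principal adherence analysis beside it:

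- **Model:** two-stage least squares, with randomised arm as instrument and baseline Time Use Survey score as covariate.
- **Exposure:** met a volunteer at least once, taken from the meeting log. Patients who improve and then stop meeting remain classed as exposed.
- **Population:** all randomised patients with outcome data, under the same missing-data handling as the intention-to-treat analysis.
- **Stated assumption:** allocation affects outcome only through meeting a volunteer (the exclusion restriction). Say how coordinator contact, the quarterly meet-ups and booklet delivery bear on it. The intervention arm gets the booklet at the introductory meeting and controls get it at a separate researcher meeting, so a never-matched patient may be treated differently by allocation alone.
- **Secondary version:** number of meetings as exposure, labelled as assuming a linear dose effect.

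If a per-protocol analysis is kept, define its set in both arms, say that the bias can go either way, and reconcile it with the sentence that places all analyses under intention to treat.

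The cost is some plan wording and one standard model; the exposure data are already being collected. The downside is a wider interval, about 1.4 times that of intention to treat at 70% exposure, and dependence on the assumptions above.
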